## Abstract

**Background:**

Obesity is often comorbid with depression and individuals with this comorbidity fare worse in behavioral weight loss treatment. Treating depression directly prior to behavioral weight loss treatment might bolster weight loss outcomes in this population, but this has not yet been tested in a randomized clinical trial.

**Methods and design:**

This randomized clinical trial will examine whether behavior therapy for depression administered prior to standard weight loss treatment produces greater weight loss than standard weight loss treatment alone. Obese women with major depressive disorder (N = 174) will be recruited from primary care clinics and the community and randomly assigned to one of the two treatment conditions. Treatment will last 2 years, and will include a 6-month intensive treatment phase followed by an 18-month maintenance phase. Follow-up assessment will occur at 6-months and 1- and 2 years following randomization. The primary outcome is weight loss. The study was designed to provide 90% power for detecting a weight change difference between conditions of 3.1 kg (standard deviation of 5.5 kg) at 1-year assuming a 25% rate of loss to follow-up. Secondary outcomes include depression, physical activity, dietary intake, psychosocial variables and cardiovascular risk factors. Potential mediators (e.g., adherence, depression, physical activity and caloric intake) of the intervention effect on weight change will also be examined.

**Discussion:**

Treating depression before administering intensive health behavior interventions could potentially boost the impact on both mental and physical health outcomes.

**Trial registration:**

NCT00572520

## Background

Obesity is a serious public health threat in the United States with 32.2% of the population affected [1]. Links between obesity and depression have been observed in clinical and epidemiological studies, particularly among women. In one clinic sample, 34% of treatment-seeking obese women were found to have major depressive disorder (MDD) [2]. This is concerning because depression is associated with worse outcomes in behavioral weight loss treatment [2]. However, the vast majority of randomized clinical trials testing obesity treatments either exclude individuals who are clinically depressed [3,4] or do not assess depression status [5-9]; thus evidence for the efficacy of behavioral weight loss treatments for depressed, obese individuals is lacking. Given the concurrence of depression with obesity and the difficulty depressed individuals have losing weight, behavioral weight loss treatments that address the unique needs of this population are needed.

A comorbid relationship between obesity and depression suggests that the two conditions may have related mechanistic pathways, which could have implications for treatment. Obesity is associated with anhedonia [10], a reduced capacity to experience pleasure, which is also a primary symptom of MDD [11,12]. Obese women appear less able to elicit pleasure from ordinarily pleasurable experiences compared to their lean counterparts [10]. When comorbid with depression, obesity may be in part attributable to maladaptive mood regulatory habits involving overeating and inactivity. Targeting weight loss through dieting could thwart this mood regulatory process by facilitating feelings of deprivation, causing compensatory overconsumption and worsened depressive symptoms. Treatments for depression in the context of obesity should directly address the links between mood, eating, and active versus sedentary behaviors, but traditional behavioral weight loss treatments were not necessarily designed to target this combination of issues, and neither were depression psychotherapies. However, behavioral treatments for depression that address maladaptive mood regulatory habits may be helpful in the context of obesity, to the extent that eating behavior and inactivity can be specifically targeted.

A treatment emanating from behavioral theory, behavioral activation [12,13], aims to increase exposure to the positive consequences of healthy behavior, for the purpose of increasing engagement in healthy behaviors, reducing engagement in depressive behaviors and decreasing avoidance behavior[13,14]. The focus of behavioral activation on increasing healthy activity and eliminating avoidance is appropriate to the treatment goals of depression and obesity. Weight loss could be facilitated by increasing an individual's arsenal of mood regulatory behaviors to break an over reliance on eating for coping with negative moods, and to gradually adopt more physically active coping behaviors. Avoidance by obese patients can take the form of excessive eating or prolonged sedentary activities that prevent engagement in other more reinforcing and active aspects of life. Increasing coping behaviors that are physically active or incompatible with eating may help to reduce avoidance behavior, depressive symptoms, and ultimately weight.

The efficacy of behavioral activation for depression has been demonstrated in a variety of populations and settings [15-18]. In a pilot study, our group demonstrated reductions in depression, good treatment adherence, and high treatment satisfaction for an intervention that delivered behavioral activation simultaneously with a brief nutrition counseling intervention [19]. However, in that study, average weight loss was modest and the greatest losses were observed in the latter weeks of treatment, after depressive symptoms had improved. Improving depressive symptoms prior to an intensive dietary intervention might be a more effective sequence of treatment delivery for weight loss outcomes in women with depression.

### Research Goals

The present study aims to compare the efficacy of a sequential two-part treatment, behavioral activation for depression followed by standard weight loss treatment (BA), to standard weight loss treatment that is not accompanied by depression counseling (ST) on weight change in depressed, obese women. The primary hypothesis is that participants in the BA condition will achieve greater weight loss than participants in the ST condition at 6-months and 1- and 2-year follow-up. Secondary research goals include comparing groups on change in depression, physical activity, daily caloric intake, psychosocial variables (emotional eating, quality of life), and cardiovascular risk factors (blood pressure, serum lipids, C-reactive protein and waist circumference) at 6-months and 1- and 2-year follow-up. Additionally, potential mediators (treatment adherence, depression, physical activity, caloric intake) of the intervention effect on weight change will be tested.

## Methods

### Study Design

This is a randomized controlled trial where obese participants with MDD are randomized to one of two treatment conditions: BA or ST. All procedures and material were approved by the University of Massachusetts Medical School's Internal Review Board.

### Eligibility Criteria

Women between the ages of 21 and 65 years old who meet criteria for obesity and MDD will be recruited. Table 1 summarizes the inclusion and exclusion criteria. Exclusion criteria were derived to: 1) minimize adverse effects of the intervention (e.g., physical limitations, does not receive physician clearance); 2) decrease error associated with the primary outcomes (e.g., taking weight loss medication or medications that influence weight); 3) prevent missing data (e.g., plans to move, no telephone) and 4) prevent participants who may require more intensive or more appropriate psychological intervention from enrolling in the study (e.g., active suicidal ideation, bipolar disorder, psychotic disorder). Participants who have been taking antidepressant medications (ADM) for more than 3 months and have no plans to change the regimen will be eligible. While participants who are on ADM will not be excluded, those in psychotherapy will be excluded because of potential conflicting therapeutic goals and possible contamination in the no therapy condition.

**Table 1 T1:** Participant eligibility and exclusion criteria.

**Eligibility Criteria**	
	Female
	Major depressive disorder
	Age: 21–65 years
	Body mass index: 30–40 kg/m^2^
	
**Exclusion Criteria**	
	Unable/unwilling to provide informed consent
	Plans to move out of area during study period
	Smoker
	Bipolar, psychotic, or post-traumatic stress disorder, bulimia
	Severe depression: HDRS > 24 or BDI-II >29
	Type 1 or 2 diabetes
	Had or plans to have bariatric surgery
	No telephone
	Unable to walk unaided or cannot walk 1/4 mile without stopping
	Does not have written clearance from primary care provider for study participation
	Has a medical condition which precludes dietary changes
	Has medical conditions likely to limit lifespan
	Taking prescription weight loss medications
	Initiated anti-depressant medication within the previous 6 weeks
	Active suicidal ideation
	Psychiatric hospitalization in the past 12 months
	Currently in psychotherapy
	Taking mood stabilizers, anti-psychotic medication or medications known to affect appetite and/or weight

Note. HRSD = Hamilton Rating Scale for Depression; BDI-II = Beck Depression Inventory-II.

### Recruitment

A computerized Patient Health Care Information System used in the University of Massachusetts Memorial (UMM) primary care clinics will identify participants who are potentially eligible using age, female gender, and body mass index ranges. Candidates will be contacted via an introductory letter signed by their primary care physician and the principal investigator (PI). Candidates will be given the opportunity to opt out by phone, or be phoned for an initial telephone screening two weeks after receiving the letter. Participants will also be recruited from the community via media outlets, the medical center intranet, and community flyers. Minority populations will be targeted by distributing flyers to businesses and health clinics that serve predominately minority populations and using advertisements in media outlets that have a large minority audience base. Free seminars about women's health will also be conducted at local businesses, community organizations, and churches to facilitate recruitment.

### Screening Process and Informed Consent

Initial eligibility will be assessed by phone and pre-eligible participants will be invited to the study visit for a screening appointment where informed consent will be obtained and eligibility will be further assessed. The Structured Clinical Interview for the Diagnostic and Statistical Manual-IV [20] will be administered to confirm the diagnosis of MDD. Eligible participants will then complete a baseline assessment visit, for which they will receive $50 (see Table 2 for the list of screening and baseline measures). Those not qualifying will receive referrals to weight loss and/or depression treatment, when applicable.

**Table 2 T2:** List of measures and frequency.

	Screening	Baseline	Month 6	Year 1	Year 2
Structured Clinical Interview for DSM-IV	X		X	X	X
Hamilton Rating Scale for Depression	X	X	X	X	X
Beck Depression Inventory	X	X	X	X	X
Medical History Questionnaire	X		X	X	X
Brief Medication Questionnaire	X		X	X	X
Body weight	X	X	X	X	X
Height	X				
Waist and hip circumference		X	X	X	X
Blood pressure		X	X	X	X
Fasting blood: Cholesterol, LDL, HDL, triglycerides, C-reactive protein		X	X	X	X
Three 24-hour dietary recalls		X	X	X	X
Three 24-hour physical activity recalls		X	X	X	X
Fawcett-Clark Hedonic Capacity		X	X	X	X
Short-form 36 Health Survey		X	X	X	X
Dutch Eating Behavior Questionnaire		X	X	X	X
Paffenbarger Physical Activity Questionnaire		X	X	X	X
Environmental Reward Observational Scale		X	X	X	X

Note. DSM-IV = Diagnostic and Statistical Manual of Mental Disorders, Fourth Edition; LDL = low-density lipoprotein; HDL = high-density lipoprotein

### Randomization

After completing the baseline visit and 24 hour diet and physical activity recalls, participants will be randomized to the BA or ST condition. Participants will be stratified into 4 strata of possible combinations of ADM (2: present, absent) × MDD severity (2: Hamilton Rating Scale for Depression (HRSD); [21]: 13–18, 19–24) at baseline. Within each strata, participants will be randomized to the two conditions in randomly permuted blocks of size 3 and 6 using the ralloc program in Stata [22]. This will ensure that the distribution of ADM status and MDD severity are approximately similar between two study conditions.

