### Sample Size Considerations and Statistical Analyses

#### Sample Size

This study will randomize 174 participants into two conditions (87 per condition) who will be followed for 2 years. We expect approximately 90% power for detecting differences in weight between the conditions assuming a weight change difference of 3.1 kg at 1-year (standard deviation = 5.5 kg) and a 25% loss-to-follow-up rate. This projected data for group differences was taken from pilot data at 6 months and projected to one year based on the original DPP weight change data. The standard deviation was a conservative value chosen from a range of successful lifestyle intervention studies [38-40].

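### Permuted blocks of 3 do not fit equal allocation to two arms, so the Randomization section conflicts with the 87 per condition behind the stated power

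*Protocol article*

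**What the plan says.** The Randomization section of the protocol article names two arms: "participants will be randomized to the BA or ST condition". It defines four strata, from antidepressant use (yes or no) and two bands of Hamilton depression score. It then gives the method: "participants will be randomized to the two conditions in randomly permuted blocks of size 3 and 6", with a named Stata program to produce the list. It states no allocation ratio.

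The Sample Size section says: "This study will randomize 174 participants into two conditions (87 per condition) who will be followed for 2 years". This is the only place that fixes the ratio, and it is 1:1. The power statement follows: "We expect approximately 90% power for detecting differences in weight between the conditions". It rests on a 3.1 kg difference at one year, an SD of 5.5 kg and loss of a quarter of the participants. Neither section states a significance level or says whether the test is one- or two-sided.

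The article mentions no third arm and no unequal allocation, and does not explain how a block of 3 is shared between two conditions.

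**The concern.** Permuted blocks hold the allocation ratio because each complete block contains the planned share of each arm. For two equal arms the block size must therefore be even. Six meets this condition and three does not. The Randomization and Sample Size sections cannot both be right as they stand.

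A reader cannot tell which one is wrong. If the list was built at 2:1, the per-arm count and the power statement are wrong. If it was built at 1:1, the reported block sizes are wrong. Some power may be at stake, and so may the tightness of balance within strata. In either case the article does not describe an allocation scheme that could be reproduced.

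**Working it through.** **Inputs.** Sample Size section: 174 randomized, 87 per condition; difference 3.1 kg at 1 year; SD 5.5 kg; "a 25% loss-to-follow-up rate". Randomization section: two arms, four strata, block sizes 3 and 6. Assumed, because it is not stated: two-sided alpha of 0.05, with one-sided 0.05 shown as the range.

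**Step 1: reproduce the stated power at 1:1.** Evaluable per arm: 87 × 0.75 = 65.25. Standard error of the difference: 5.5 × √(1/65.25 + 1/65.25) = 0.963 kg. Non-centrality: 3.1 / 0.963 = 3.22. Two-sided power is 89.2% by non-central t (89.6% by normal approximation), which matches the claimed figure of roughly 90%. One-sided 0.05 gives 94%, a poorer match. The power statement therefore fits equal arms and a two-sided 5% test.

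**Step 2: what the block sizes allow.**
- Size 3: the splits that use both arms are 2+1 and 1+2. None is equal.
- Size 6: 1+5, 2+4, 3+3, 4+2, 5+1. Only 3+3 is equal.
- The only fixed ratio that both sizes share is 2:1 or its reverse (2+1 with 4+2). At a fixed 1:1 ratio a block of 3 cannot be built.

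**Step 3: the fixed 2:1 reading.** 174 × 2/3 = 116 and 174 × 1/3 = 58. Evaluable: 116 × 0.75 = 87 and 58 × 0.75 = 43.5. Standard error: 5.5 × √(1/87 + 1/43.5) = 1.021 kg. Non-centrality: 3.1 / 1.021 = 3.04. Two-sided power is 85.4% (85.9% by normal approximation). One-sided it is about 92%.

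Reaching 90% at 2:1 would need 150 evaluable women by normal approximation, or 150 / 0.75 = 200 randomized.

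**Step 4: readings in which blocks do not share one ratio.** The article describes neither of these.
- *Blocks of 3 always 2+1, blocks of 6 always 3+3, in equal numbers.* Each pair of blocks gives 5:4, so 174 × 5/9 ≈ 97 and 174 × 4/9 ≈ 77.
- *Blocks of 3 with direction chosen at random, blocks of 6 at 3+3.* The arms are equal on average. In a simulation with four equally likely strata (an assumption), the SD of the difference in arm size was about 5 and the 95th percentile of its absolute value was 10, which corresponds to 92:82.

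| Split of 174 | Evaluable after 25% loss | Power, two-sided 5%, non-central t |
|---|---|---|
| 87:87 | 65.25 : 65.25 | 89.2% |
| 92:82 | 69 : 61.5 | 89.1% |
| 97:77 | 72.75 : 57.75 | 88.8% |
| 116:58 | 87 : 43.5 | 85.4% |

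**Step 5: even blocks for comparison.** Under the same strata assumption, randomly chosen blocks of 4 and 6 gave an SD of the difference of about 2, against about 5 for blocks of 3 with random direction. Exact 87:87 occurred in about 39% of runs, because the last block in each stratum is usually incomplete.

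**The case against.** The best defence accepts the parity problem and disputes how far it reaches. Four parts of it stand.

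First, a reader might infer that the scheme must either produce 116:58 or be impossible to run. The article does not support that. It states no ratio and does not say that all blocks share one, so 116:58 is an inference under the usual construction. Nor does it say how the named allocation program treats such sizes, so nothing here rests on that.

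Second, a reader might infer that the stated power is lost on every reading. It is not. With 97:77 or 92:82, power stays near 89%, and the article claims only about 90%.

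Third, a reader might infer that balance on antidepressant use and severity is undermined in general. The article's claim concerns similar distributions in the two arms, and a fixed 2:1 ratio in every stratum preserves that as well as 1:1 does. Balance is looser only where blocks depart from a common ratio.

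Fourth, 87 per condition is a target under any stratified blocked scheme, and even blocks do not guarantee it either. The block sizes may also be a reporting slip in a condensed article, with a sound list behind it.

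None of this removes the inconsistency. The article commits itself to the number of arms, the block sizes and the per-arm count, and these do not fit together. A fuller protocol could show which is wrong, but could not make all of them right.

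**Conclusion.** The point holds as an internal contradiction. Blocks of 3 cannot deliver the 1:1 allocation on which the Sample Size section rests, and the article supplies neither an unequal ratio nor a rule for odd blocks.

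The numerical cost is modest. The worst case, a fixed 2:1 ratio throughout, lowers power by about 4 points, from about 89% to about 85%; at one-sided 5% the fall is from 94% to about 92%. On the other readings examined, power is essentially unchanged and the cost is looser balance of arm sizes within strata. None of these readings in itself biases the treatment comparison.

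The figures assume the article's 3.1 kg, SD 5.5 kg and 25% loss, the same loss in both arms, and an alpha that the article does not state.

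**What to change.** Reconcile the Randomization and Sample Size sections.

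- **If 1:1 is intended**, as the per-arm count and the power figure indicate: state the ratio and replace the block sizes with even ones, for example randomly chosen 4 and 6, within the four strata. Check the allocation list actually in use. If it was built with blocks of 3, regenerate it before allocation goes further. If it already used even blocks, only the sentence needs correcting.
- **If 2:1 is intended**: state the ratio and which arm is larger, replace 87 per condition with 116:58, and restate power as about 85%, or raise the total to about 200 to keep 90%.

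In either case, state alpha and sidedness beside the power figure. The first option costs one sentence and possibly a new list, with no extra participants.

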### Outcomes and Study Measures

The main study outcome will be body weight measured using the digital Tronix scale, with the participant wearing only light clothing and no shoes. Body weight will be measured at every study visit, but analyses will focus primarily on change in body weight from baseline to the 6-months and 1- and 2-year follow-up.

Secondary outcomes include depression (HRSD and Beck Depression Inventory-II (BDI-II); [23]), physical activity and dietary intake, other psychosocial variables (emotional eating, quality of life), and cardiovascular risk factors (blood pressures, serum lipids, C-reactive protein) at 6-months and 1- and 2-year follow-up.

Treatment adherence data will also be collected at all assessment time points to examine possible mechanisms of the effect of the BA intervention on body weight. Additional potential mediators include caloric intake, physical activity and depression (see Table 2 for a complete list of study measures and the timing of these measures).

### Intervention

Both ST and BA conditions will involve an Intensive Treatment and a Maintenance phase. The Intensive Treatment phase will last 6-months and involve 26 sessions. Ten sessions will be 1-hour individual visits, and 16 sessions will be 1.5-hour group behavioral weight loss visits conducted by a registered dietitian or exercise physiologist. The timing of the individual and group visits varies between the two conditions. In the BA condition, participants will begin with 10 weekly individual visits of behavior therapy for treatment of depression, with the initial group behavioral weight loss visits starting on week 9. Participants in the ST condition will begin both the group behavioral weight loss visits and individual health education visits on week 1 (see Tables 3 and 4 for the timing of individual and group sessions in each condition) for two reasons. First, paralleling the BA condition (i.e., first 8-weeks of individual visits of health education attention control only) could lead to differential attrition rates since ST participants may not stay engaged when active treatment is delayed for 8 weeks. Second, this approach is also more consistent with usual care, in which participants would be enrolled and begin treatment immediately.

**Table 3 T3:** Distribution of treatment sessions by condition during the first 12 weeks of the 6-month Intensive Treatment phase.

Week	**1**	**2**	**3**	**4**	**5**	**6**	**7**	**8**	**9**	**10**	**11**	**12**
**ST**	I/G	G	G	G	I/G	G	G	G	G	G	I	G
**BA**	I	I	I	I	I	I	I	I	I/G	I/G	G	G

Note. ST = Standard treatment; BA = Behavioral Activation; I = Individual visit; G = Group visit

**Table 4 T4:** Distribution of treatment sessions by condition during the second 12 weeks of the 6-month Intensive Treatment phase.

Week	**13**	**14**	**15**	**16**	**17**	**18**	**19**	**20**	**21**	**22**	**23**	**24**
**ST**	I	G	I	G	I	G	I	G	I	G	I	I
**BA**	G	G	G	G	G	G	G	G	G	G	G	G

Note. ST = Standard treatment; BA = Behavioral Activation; I = Individual visit; G = Group visit

The 18 month Maintenance phase will consist of 6 monthly 90-minute group sessions and 6 monthly 20-minute counseling phone calls by their therapist or health education counselor, depending on their condition assignment. Then, participants will receive 20-minute counseling phone calls once every 3 months for one year. All visits in both phases will be audiotaped for quality assurance.

